### Control arm

Patients randomized in the control arm will be treated with a full ERAS protocol that establishes oral food “at will” after the operation. In case of occurrence of any complication impairing the full recovery of oral food within postoperative day 5, patients may receive parenteral or enteral nutrition as clinically indicated.

### Procedures common to both arms

Patients of both groups will be treated according to the ERAS Society guidelines for perioperative care for PD (Table 1) (8). Blood glucose ≥180 mg/dl will be treated with insulin injection (either subcutaneous or by continuous IV infusion). Open PD technique will be chosen by the participating centers according to their standards.

### Study plan

Study plan and schedule of assessment are summarized in Table 2.

**Table 2 tab2:** Study plan and schedule of assessment.

Visit	V pre	V1	V2		V3	V4	In hosp FU	Dis	FU
Time interval	Pre random	Basal at random	Intraoperative	Day 1	Day 3	Day 5	Once a day during index hospitalization	Discharge	3-mo. follow-up (from the day of surgery)
Informed consent	X								
Demographics	X								
Height	X								
Weight	X							X	X
Body mass index	X								
Physical examination (every day until discharge)	X			X	X	X	X	X	X
Patient history	X								
Inclusion criteria		X							
Exclusion criteria		X							
Blood pressure		X	X		X	X	X		
Heart rate		X	X		X	X	X		
ECG		X							
ICU admission							X		
Lab tests*		X		X	X	X	X	X	
Need of insulin			X	X	X	X	X	X	X
NRS-2002		X							
Death			X	X	X	X	X	X	X
Safety endpoints				X	X	X	X	X	X
Blood loss			X						
Duration of surgery			X						
Surgical details			X						
Fluid balance			X	X	X	X	X		
Histology			X					X	
Analgesia			X	X	X	X		X	
Discharge criteria						X	X		
Complications (CCI)				X	X	X	X	X	X
Drug administration (DAY 1-5)				X	X	X			

*Urea, Creatinine, Complete blood count, PT, PTT, Glucose, Na, K, Cl, prealbumin, albumin, glycate haemoglobin, bilirubin, CRP.

### Ethical aspects

The study has been approved by the Competent Authority (AIFA) the Ethical Committee of all participating centers. The local Ethical Committee, as coordinating center, provided the “not emendable judgement” according to the Italian legislation (approval number: 3467; date: February 11, 2022).

## Outcomes

The primary endpoint of the trial is the complication burden within 90 days after surgery. The complication burden will be assessed by the Comprehensive Complication Index (CCI) (15), that incorporates all complications and their severity as defined by the Clavien-Dindo classification, and summarizes postoperative morbidity with a numerical scale ranging from 0 (no complication) to 100 (death).

### Hypothesis tested

#### H0 hypothesis

The administration of a parenteral nutrition added to the ERAS protocol will not affect the CCI as compared to standard of care (ERAS).

#### H1 hypothesis

The administration of a parenteral nutrition added to the ERAS protocol will positively affect the CCI as compared to standard of care (ERAS).

Secondary outcome measures will be:

- Actual daily calories delivered by PN.- Rate of unplanned artificial nutrition (for control group).- Rate and severity of complications at 90 days after discharge.- Rate of surgical site infections (16)- The rate and severity of postoperative pancreatic fistula (17)- Rate and severity of DGE (18)- Rate and severity of hemorrhage (19)- Length of stay (LOS) based on predefined criteria- Actual LOS- Rate of reoperation.- Rate and duration of intensive care treatment.- Rate of hyperglycemia (blood glucose >180 mg/dl)- Use of insulin (subcutaneous bolus or continuous infusion)- Δ plasma prealbumin levels (baseline, postoperative day 1 and 6)- Use of morphine- Readmission rate- Body weight (90 days)- 90-day mortality

Any attending surgeon will decide the day of discharge according to his individual clinical judgement. However, LOS will be also calculated by the achievement of pre-specified discharge criteria (full patient mobilization, pain controlled by oral therapy, full tolerance to oral feeding). In particular, a visual analog pain scale ≤2 must be achieved for safety discharge.

Post-discharge follow-up will be accomplished by weekly outpatient visits. Also telephone interviews will be allowed to monitor patient health state, but in case of warning signs or symptoms of a complication, patients will be asked to refer to the hospital where the operation was performed for further clinical evaluation.

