### Study duration and definition of termination

The expected duration of enrolment is approximately 2 years.

The study will be considered as terminated when the last enrolled patient will have completed the 90-day follow-up after the date of surgery.

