### Case report form

The following baseline patient-related parameters will be recorded:

- Age (years)- Sex- Weight (kg)- Height (m)- Body mass index (kg/m^2^)- Nutritional risk score-2002- Percent of weight loss in the 6 months prior to surgery- Charlson comorbidity index- Diabetes- Jaundice- Biliary stenting- Routine laboratory test (albumin, preabumin, bilirubin, hemoglobin, creatinine, HbA1c, CRP)- Primary disease with indication to surgical resection- ASA score- Neoadjuvant treatments

The following intraoperative parameters and events will be recorded:

- The day of operation- Type of surgical procedure (PPPD, Whipple)- Type of pancreatic anastomosis (gastric, jejunal)- The level of intraoperative contamination (clean; clean-contaminated; contaminated; dirty)- Use of epidural analgesia, TAP block, subfascial catheter- Intraoperative hypothermia (defined as body temperature < 35.5°C for more than 30 min)- Estimated blood loss (mL)- Volume of IV fluid infusion- Intraoperative blood transfusion- Fluid balance (in and out difference)- Duration of operation (minute)- Main pancreatic duct diameter- Pancreas texture (soft, intermediate, hard)- Fistula risk score

After the operation the following parameters and events will be recorded:

- Capillary blood glucose levels (every 6 h for 5 consecutive days)- Any administration of insulin (for blood glucose ≥180 mg/dL)- Occurrence of a complication (90-days)- Type of complication- The complication burden according to CCI (90-day)- The severity of complication according to Clavien-Dindo classification- The need of reoperation, reason and postoperative day- The need of unplanned intensive care treatment and the duration (days)- The day of canalization to gas and stools- The day of resumption of oral feeding- The need and duration of artificial nutrition (for the control arm)- Potential hospital discharge according to predefined criteria- The actual day of hospital discharge- Disease staging- Readmission rate (30-day)- Mortality rate (90-day)

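### One secondary complication outcome is timed from discharge, while the stated complication window, last visit and trial end run from surgery

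*Protocol article*

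**What the plan says.** Under the H1 hypothesis heading, where the secondary outcomes are listed, one item reads "Rate and severity of complications at 90 days after discharge". No other item in that list is counted from discharge.

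The places that state an anchor for the complication window or for follow-up all use surgery:

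- **Primary endpoint (Outcomes; the abstract agrees):** "The primary endpoint of the trial is the complication burden within 90 days after surgery".
- **Last scheduled contact (Study plan, Table 2):** the final column is headed "3-mo. follow-up (from the day of surgery)", and complications (CCI) are ticked there.
- **End of trial (Study duration and definition of termination):** "The study will be considered as terminated when the last enrolled patient will have completed the 90-day follow-up after the date of surgery".

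Two further places bear on the point without settling it. The Case report form section lists "Occurrence of a complication (90-days)" with no anchor. The text after the secondary outcomes says "Post-discharge follow-up will be accomplished by weekly outpatient visits", adds telephone contact, and gives no end date for either.

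**The concern.** An outcome timed from discharge does not fit a follow-up schedule timed from surgery. Two different problems can follow, depending on how the conflict is resolved in practice.

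- **Follow-up stops at day 90 after surgery, as Table 2 implies.** The outcome as defined is then incomplete at its far end for every patient discharged alive, by as many days as that patient stayed in hospital.
- **Follow-up is stretched to 90 days after discharge.** The period at risk, counted from surgery, then differs between patients. Its length depends on something that happens after randomisation. The article leaves the discharge day to the attending surgeon, says under Screening and randomization processes that surgeons are not blinded, and lists length of stay as a secondary outcome. If stay differs by arm, the arms are observed for different lengths of time.

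The wording also leaves open whether complications before discharge count, and a patient who dies in hospital has no discharge date from which to count.

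**Working it through.** The article gives no figure that depends on this window, so there is nothing to reproduce. The check is date arithmetic.

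**Inputs**

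- Window in the secondary outcome: 90 days from discharge (secondary outcome list).
- Last scheduled contact: 3 months from surgery, taken as day 90 (Table 2, with the termination section).
- Discharge day L after surgery: not given. This is an assumption, with 8 to 20 days as the main range and 5 to 30 days as a wider one.

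**Formulas**

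- Day on which the window closes, counted from surgery: 90 + L.
- Days beyond scheduled follow-up: (90 + L) − 90 = L.
- Uncovered share of a window that starts at discharge: L/90.
- Post-discharge days that are covered: 90 − L.

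**Results**

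| Assumed L (days) | Window closes on day | Days uncovered | Share L/90 | Post-discharge days covered |
|---|---|---|---|---|
| 5 | 95 | 5 | 5.6% | 85 |
| 8 | 98 | 8 | 8.9% | 82 |
| 14 | 104 | 14 | 15.6% | 76 |
| 20 | 110 | 20 | 22.2% | 70 |
| 30 | 120 | 30 | 33.3% | 60 |

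If the item is read as running from surgery to 90 days after discharge, the window is 90 + L days long. The uncovered share becomes L/(90 + L): 8/98 = 8.2% at 8 days and 20/110 = 18.2% at 20 days. The conclusion does not depend on which reading is taken.

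**If follow-up did run to 90 days after discharge.** The period from surgery would be 90 + L days, so a difference of d days in mean stay between the arms becomes a difference of d days in mean observation time. For a hypothetical d = 2, that is 2/90 = 2.2% of a 90-day window.

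**With the outcome anchored at surgery.** The window closes on day 90 for everyone, and the uncovered part is 0 days whatever the stay.

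**The case against.** The strongest reply is that this is probably a slip of one word, in one item of a long secondary list, in a condensed article. That may well be so. Nothing in the article corrects it, however, and it is a stated outcome definition rather than a detail left out for brevity.

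Several stronger readings are tempting, and the document does not support them:

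- **That the outcome cannot be observed.** Most of it can. Complications up to day 90 after surgery are recorded, and only the last L days fall outside the schedule. The weekly visits have no stated end, and the termination rule refers to the last enrolled patient, so earlier patients might be seen beyond day 90. But no visit is scheduled for that purpose, and Table 2 ends at 3 months from surgery.
- **That both problems occur together.** They belong to alternative resolutions. If observation stops at day 90 after surgery, the arms have the same planned period from surgery. If it runs to 90 days after discharge, the tail is not missing.
- **That every 90-day item is counted from surgery.** Body weight, mortality and the case report form entry for complications carry no anchor. The statement holds only for the places that give one.
- **That the outcome is meant to break down the primary CCI and cannot be reconciled with it.** No such purpose is stated, and rate and severity to day 90 after surgery can be obtained from the planned records.
- **That "Readmission rate (30-day)" on the case report form is a further contradiction.** The outcome list names readmission without a window and the form supplies one. The two are compatible, and a longer window would be a preference.

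It is also fair to say that L/90 is a share of calendar time. The article does not show what share of complications would fall in those days.

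**Conclusion.** The inconsistency is real and limited. As defined, one secondary outcome runs past scheduled follow-up by each patient's length of stay: about 9% to 22% of the window for an assumed stay of 8 to 20 days, and 5.6% to 33.3% over 5 to 30 days. The direction is certain for any stay above zero; the size rests on the assumed stay and on taking 3 months as day 90. Extending observation to match the definition would instead tie the risk period to a post-randomisation event in an open-label trial.

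The primary endpoint is correctly anchored, and the sample size and type I error do not depend on this item. The point is worth correcting before analysis because it decides which events are counted.

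**What to change.** Restate the secondary outcome as the rate and severity of complications within 90 days after surgery, so that it agrees with the primary endpoint, Table 2 and the termination rule. Print the same anchor beside the complication entry on the case report form.

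The cost is a one-line amendment and one label. No visit is added, and no sample size or power figure changes.

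The alternative is to keep the discharge anchor, schedule a visit at 90 days after discharge and move the end-of-study definition to match. That costs more and leaves the window dependent on length of stay. The readmission window needs no change on this account.

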## Statistical planning

The sample size of 120 patients per group is necessary to provide an 80% power to detect at least a 30% reduction in the CCI, which is expected to be around 23 (median) (IQR 21–31) or mean 27 (±20 SD) in complicated patients of the control group. The hypothesized reduction of 30% is based on sound clinical relevance meaning that such reduction will have a consistent and significant impact of the postoperative course with advantages on well-being, quality of life, shorter length of hospitalization and a relevant reduction of heath care burden and resources. The median CCI of 23 is retrieved from a previous publication (20). The rate of complication in this type of surgery is expected to be approximately of 60%.

A Mann–Whitney test is considered, type I error rate is fixed at 5% (two tails) and an expected drop-out of 10% is taken into account.

For the binary end-points, the relative risk (RR) with the corresponding 95% confidence interval, comparing the two groups, will be estimated. For the primary end-point, also the risk difference (RD) will be computed. For the numerical end-points the difference in the location parameter (i.e., median pairwise difference) between the two groups with the corresponding 95% confidence interval will be computed. Fisher test and Mann–Whitney test will be adopted to evaluate univariate associations. Incidence of complications over time in the two groups will be described according to the Nelson-Aalen cumulative hazard estimator also accounting for multiple events per patient. The incidence in the two groups will also be compared by computing the incidence rate ratio (with 95% confidence interval). This analysis will be performed both considering all complications and only major complications.

A multivariate quantile regression model (focused on median, 25^th^ and 75^th^ percentiles) will be used to identify factors associated with the primary endpoint and to evaluate the effect of treatment adjusting for possible residual confounding. Logistic regression will also be used to model the probability of CCI >23. Using these regression models, the effect of PN over controls on the CCI will be also investigated within pre-specified subgroups to account for possible effect modification. The pre-specified risk factors for this analysis will be:

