- Nutritional risk screeing-2002 (≥3)- Body mass index (> 30)- Sex (male)- Age (>70 years)- Charlson comorbidity index (>4)- ASA score (=3)- Blood loss (≥500 mL)- Duration of surgery (>360 min)- Biliary stenting- Diabetes- Pylorus-preserving PD (vs. Whipple)- Pancreatic ductal carcinoma (vs. others)- Fistula risk score (≥7)- ERAS overall compliance (>70%)

All analyses will be done based on the principles of “intention-to-treat” and “per-protocol” and performed with the R software.

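### Comparing the change in prealbumin without baseline adjustment is valid, but less precise than comparing the day-6 value adjusted for the baseline already collected

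*Protocol article*

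**What the plan says.** In the protocol article, the list of secondary outcomes under the H1 hypothesis heading includes "Δ plasma prealbumin levels (baseline, postoperative day 1 and 6"). It does not say whether the change is absolute or relative, or which pair of time points defines it.

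Statistical planning sets one rule for all numerical endpoints. The estimate is given by "For the numerical end-points the difference in the location parameter (i.e., median pairwise difference) between the two groups", with a 95% confidence interval. For testing, "Fisher test and Mann–Whitney test will be adopted to evaluate univariate associations". Neither takes a covariate.

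Regression is planned only for the Comprehensive Complication Index (CCI): the quantile model "will be used to identify factors associated with the primary endpoint and to evaluate the effect of treatment adjusting for possible residual confounding", and the logistic model is for a CCI above 23. The risk factors listed for these models begin with "Nutritional risk screeing-2002 (≥3") and do not include baseline prealbumin.

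Baseline prealbumin is collected. The Case report form section lists, among the baseline parameters, "Routine laboratory test (albumin, preabumin, bilirubin, hemoglobin, creatinine, HbA1c, CRP"). The laboratory panel under Table 2 (Study plan) is "Urea, Creatinine, Complete blood count, PT, PTT, Glucose, Na, K, Cl, prealbumin, albumin, glycate haemoglobin, bilirubin, CRP". It is marked at the basal visit, on days 1, 3 and 5, daily in hospital, and at discharge.

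**The concern.** Subtracting the baseline value fixes its slope at 1, whatever the data show. A major resection lies between baseline and day 6, so the true slope may be well below 1. In that case the subtraction adds noise from the baseline measurement instead of removing it. Regression on baseline estimates the slope and avoids this.

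What is at stake is precision on one secondary outcome. Prealbumin is the only laboratory marker of nutritional status among the listed outcomes, so a needlessly wide interval would be a pity. The sample size was set for the CCI, which leaves efficiency of analysis as the practical way to sharpen this comparison.

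**Working it through.** **Inputs.** The article states no standard deviation, correlation, effect size or power for prealbumin, so there is no figure to reproduce. The number of patients comes from Statistical planning: 120 per group with 10% drop-out, hence 120 × 0.90 = 108 evaluable per arm. Everything else is assumed and varied. Let s0 and s1 be the baseline and day-6 standard deviations, and rho their correlation. The change is taken as baseline to day 6 on the absolute scale.

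**Step 1: direction.**
- Change score: s0² + s1² − 2·rho·s0·s1
- Day-6 value adjusted for baseline: s1²·(1 − rho²)
- Difference: s0² − 2·rho·s0·s1 + rho²·s1² = (s0 − rho·s1)²

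A square is never negative, so under a linear model the change score is never the more precise. The two are equal only when s0 = rho·s1, that is, when the true slope on baseline is 1.

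**Step 2: size with equal standard deviations.** The ratio of adjusted to change-score variance is (1 − rho²) / [2(1 − rho)] = (1 + rho)/2.

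| Assumed rho | Adjusted/change variance | Reduction | 108 per arm on change scores is worth, with adjustment |
|---|---|---|---|
| 0.3 | 0.65 | 35% | about 70 per arm |
| 0.5 | 0.75 | 25% | 81 per arm |
| 0.7 | 0.85 | 15% | about 92 per arm |
| 0.9 | 0.95 | 5% | about 103 per arm |

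The last column is 108 × (1 + rho)/2. The change score has 2(1 − rho) times the variance of the day-6 value alone, so below rho 0.5 it is noisier than ignoring baseline altogether.

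**Step 3: unequal standard deviations.** With k = s0/s1, the ratio of change-score to adjusted variance is (1 + k² − 2·rho·k)/(1 − rho²). For k from 0.7 to 1.5 and rho from 0.3 to 0.7 it runs from 1.00 (k = 0.7, rho = 0.7: 0.51/0.51) to 2.58 (k = 1.5, rho = 0.3: 2.35/0.91).

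**Step 4: does it carry over to the rank test?** A simulation used 108 per arm, normal data, equal standard deviations and 4,000 runs. The effect was chosen so that the adjusted analysis has 80% power. Mann-Whitney on the change score reached 58%, 65% and 72% at rho 0.3, 0.5 and 0.7, against 79–80% for analysis of covariance (ANCOVA). The 80% is a reference point chosen for the comparison, not a property of this trial's prealbumin endpoint.

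**The case against.** The strongest reply is that nothing here is an error. Randomisation makes the unadjusted comparison of change scores valid, and the same efficiency remark could be made of almost any change-score endpoint. The rule is also generic: no sentence names prealbumin as analysed by Mann-Whitney, the contrast behind the Δ is not stated, and a statistical analysis plan that is not shown may refine the method. These limits stand and keep the point small. They do not remove it, because the article states both the form of the endpoint and a covariate-free method for every numerical endpoint. That is a stated choice, not an omitted detail.

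Several stronger readings are tempting, and the article does not support them.
- *That the comparison is biased.* Chance baseline differences can carry into the change by regression to the mean. This describes imbalance in one realised sample and is the same precision point again, not a systematic error.
- *That the trial is short of power for prealbumin by a known amount.* The sentence "The sample size of 120 patients per group is necessary to provide an 80% power" concerns the CCI. No power is claimed for prealbumin, and the loss can be close to nil for some combinations of rho and standard deviations.
- *That reading the CCI result depends on prealbumin.* The article assigns it no such role. It is one of 18 secondary outcomes, and the list also has calories delivered by parenteral nutrition and 90-day body weight.

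**Conclusion.** The point holds as a modest gain in precision on a secondary endpoint. The direction follows from algebra under a linear model and needs no assumption about rho. The size does: with equal standard deviations the variance would fall by about 35%, 25%, 15% or 5% at rho 0.3, 0.5, 0.7 or 0.9, and the article cannot say which applies. The figures also assume that the intended contrast is baseline to day 6 and that the general rule for numerical endpoints governs prealbumin. The planned comparison remains valid and the primary conclusion is unaffected.

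**What to change.** State that prealbumin on postoperative day 6 will be compared between arms with baseline prealbumin as covariate. Use ANCOVA or, if the values are skewed, rank ANCOVA or median regression; quantile regression is already planned for the CCI. The stratification factors, center and neoadjuvant therapy, may be added. Report the adjusted difference with its 95% confidence interval and keep the raw change as a descriptive summary.

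Two details should be fixed in the wording.
- Do not adjust for the day-1 value. Allocation takes place on the evening of surgery or at 8 AM on day 1, and parenteral nutrition starts on day 1, so that sample may be taken after randomisation.
- Name the day-6 value, not the last available one. The panel is also marked at discharge, and a last value would fall at a different time for each patient. Table 2 has no day-6 column, so the sample relies on the daily in-hospital column and patients discharged earlier may lack it. That holds equally for the change score.

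The cost is a sentence or two of analysis wording, with no new data and no change to the sample size.
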